**Method/design:**

ATTILA (Assistive Technology and Telecare to maintain Independent Living At Home for People with Dementia) is a pragmatic, multi-centre, randomised controlled trial over 104 weeks that compares outcomes for people with dementia who receive ATT and those who receive equivalent community services but not ATT. The study hypothesis is that fewer people in the ATT group will go into institutional care over the 4-year period for which the study is funded. The study aims to recruit 500 participants, living in community settings, with dementia or significant cognitive impairment, who have recently been referred to social services.

Primary outcome measures are time in days from randomisation to institutionalisation and cost effectiveness. Secondary outcomes are caregiver burden, health-related quality of life in carers, number and severity of serious adverse events, and data on acceptability, applicability and reliability of ATT intervention packages. Assessments will be undertaken in weeks 0 (baseline), 12, 24, 52 and 104 or until institutionalisation or withdrawal of the participant from the trial.

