### Planned inclusion and exclusion criteria

#### Inclusion criteria

Participants will be people with dementia or evidence of cognitive difficulties significant enough to suggest the presence of dementia without having been formally diagnosed as having dementia, both with and without capacity. This will include those with young or later-onset dementia. Additionally, all participants must fulfil the following criteria:

• Meeting England’s eligibility criteria for access to social care services FACS (Fair Access to Care Services);

• Living in an ordinary community dwelling (including sheltered and very sheltered accommodation);

• Have a working telephone line in their home.

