### Assessments

Assessments will be undertaken by local investigators employed by the ATTILA team in weeks 0 (baseline), 12, 24, 52 and 104. All local investigators are researchers with clinical experience.

Following an assessment of mental capacity (and therefore ability to consent), confirmation of eligibility to take part, the consent process and randomisation, both groups will receive an initial assessment using the following scales: the Bristol Activities of Daily Living Scale (BADLS)
[29], Standardised Mini-mental State Exam (SMMSE)
[30,31], the Client Services Receipt Inventory (CSRI)
[32], The Model of Human Occupation Screening Tool (MOHOST)
[33] and the EuroQol EQ-5D
[34]. Unpaid carers of participants will be assessed over the same intervals using the Zarit Burden Inventory (ZBI)
[35], The Centre for Epidemiological Studies Depression Scale (CES-D10)
[36], the State Trait Anxiety Inventory (STAI-6)
[37], the Short Form Health Survey (SF-12v2)
[38] and the Carer Technology Acceptance Questionnaire (SUTAQ)
[39]. All of the outcome measures have established validity and high levels of inter- and intra-rater reliability. No pre-testing before randomisation is possible because of concerns by local authority hosts that this will delay the deployment of care and/or telecare to people who may have urgent needs for support.

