#### Cost-effectiveness

Costs will be calculated by attaching nationally applicable unit cost measures to health and social service use (collected at intervals stated above for each participant using a modified version of the CSRI), using national figures taken from the Personal Social Services Research Unit (PSSRU) annual compendium
[40] where available. The costs of ATT will be calculated anew for those services provided, and in this we will be guided by methods and experience gained in the WSD trial of telecare and telehealth
[25]. *Data on carer time and task inputs* will come from the CSRI, and will be valued using two approaches (replacement wage and opportunity cost) and then comparing the results in sensitivity analyses.

*Cost-effectiveness analyses* will be of two types to take into account the complication that the primary outcome (time to institutionalisation) is itself partly an indicator of resource use. Each type of analysis will then be conducted from each of two perspectives: for the ‘formal’ health and social care system (which is, for example, the perspective employed by the National Institute for Health and Care Excellence in England and Wales to appraise health technologies as a basis for producing clinical guidelines
[41]) and for society as a whole (which would then additionally include the value of carer time and any productivity losses from disrupted employment, either for the person with dementia or the carer).

The first type of cost-effectiveness analysis will measure costs only up to the point at which a study participant goes into a care home or hospital and not beyond (‘community costs’) and will then examine cost-effectiveness in achieving the primary outcome (days from randomisation to institutionalisation in the two year period). This analysis will show the incremental cost of community-based support for each additional institutional day avoided. The second type of analysis will measure costs for the whole 2-year period, including costs of care home and hospital stays (‘total costs’), and will then examine cost-effectiveness where the outcome is EQ-5D change, also over the 2-year period. We will also use the EQ-5D to generate Quality-Adjusted Life Year (QALY) measures by attaching societal weights
[42].

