##### Mental capacity

A diagnosis of dementia does not necessarily mean that the potential participant cannot consent to take part in the study and careful, but tactful checks will be made to establish their capacity to consent. When the person does not have capacity to consent, we will seek to identify someone known to the participant who would be prepared to act as the participant’s consultee, within the meaning of England’s Mental Capacity Act (2005).

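### The 2-year EQ-5D change behind one of the two primary cost-effectiveness analyses has no fixed respondent, no listed carer-rated series, and an unclear collection rule after placement

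*Protocol article*

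**What the plan says.** The abstract (Method/design) states: "Primary outcome measures are time in days from randomisation to institutionalisation and cost effectiveness". The Cost-effectiveness section defines two types of analysis. The first relates community costs to days before institutionalisation. The second counts all costs over 2 years, care-home and hospital stays included, and will "examine cost-effectiveness where the outcome is EQ-5D change, also over the 2-year period"; QALYs are also derived from EQ-5D.

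On who is measured and how:

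- **Inclusion criteria:** people with dementia or marked cognitive difficulty are eligible, "both with and without capacity".
- **Assessments, participants:** both groups are assessed with BADLS, SMMSE, CSRI, MOHOST "and the EuroQol EQ-5D". Neither the respondent nor the EQ-5D version is named.
- **Assessments, carers:** "Unpaid carers of participants will be assessed over the same intervals". Their scales are named one by one: ZBI, CES-D10, STAI-6, SF-12v2 and SUTAQ. No carer-rated EQ-5D on the participant is among them, and under Quality of life the SF-12v2 measures the carer's own health.
- **Assessments, measurement quality:** "All of the outcome measures have established validity and high levels of inter- and intra-rater reliability".
- **Mental capacity:** "When the person does not have capacity to consent, we will seek to identify someone known to the participant", to act as consultee. No part in outcome reporting is given to that person.
- **Abstract, Method/design:** visits are at weeks 0, 12, 24, 52 and 104, but stop earlier if the participant is institutionalised or withdraws. The Assessments section gives the same weeks without that stop.

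**The concern.** EQ-5D is the only quality-of-life scale listed for participants, and it supplies the effect side of the total-cost analysis. In a progressive illness some participants may become unable to complete it during 2 years, and some may be unable at entry. With no respondent fixed, two things can happen. The form may go unanswered, most likely for the most impaired, or someone else may start to answer it part-way. In the second case a follow-up score from one person is subtracted from a baseline score from another, and the difference includes the gap between the two raters.

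Move into a care home is a plausible point for either to happen, and it is also the event that ATT is meant to delay. A distortion tied to it could therefore differ between arms. The article plans incremental cost-effectiveness ratios and net-benefit acceptability curves, so any distortion in the incremental effect passes straight into the result.

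This cannot be left wholly to an analysis plan: a week-0 carer rating that was never taken cannot be recovered later.

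**Working it through.** **The plan's own figures.** The article gives no target difference, SD or power for EQ-5D, so there is no EQ-5D figure to reproduce. The 50% and 35% institutionalised at 2 years (Sample size calculation) are used below. They agree with the stated total of 500: two proportions at two-sided 5%, 90% power and 1:1 allocation (all three assumed, none stated) need 227 per arm, 454 in all; 454 × 1.10 gives 500 and 454 / 0.90 gives 505. That supports the rates as inputs and says nothing about EQ-5D.

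**Step 1. The passages side by side.** The total-cost analysis needs EQ-5D from week 0 to week 104, including time in a care home. Read literally, the abstract stops all assessments at institutionalisation. Both cannot be followed for a participant who is placed before week 104.

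**Step 2. If the abstract is followed.** No EQ-5D exists after placement, so no respondent can change at placement. The problem is loss. At the planned rates, week-104 EQ-5D is lost through placement for 50% of control and 35% of ATT participants. Under constant hazards, with deaths ignored, mean time at home within 730 days is p × 730 / (−ln(1 − p)):

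- Control: 0.50 × 730 / 0.693 = 526.6 days, so 730 − 526.6 = 203.4 days without EQ-5D.
- ATT: 0.35 × 730 / 0.431 = 593.1 days, so 730 − 593.1 = 136.9 days without EQ-5D.
- Difference: 66.5 days, or 66.5 / 365.25 = 0.182 years. The article states 55 days for its average delay, or 0.151 years.

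**Step 3. If EQ-5D continues after placement with a new respondent.** This is illustration only. Assume that the respondent changes exactly at placement and at no other time, with a scoring shift of 0.05 to 0.20. The shift is assumed; the document gives none.

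- Spurious arm difference in week-104 change = shift × difference in share switched. At 50% v 35%: 0.15 × 0.05 = 0.0075, up to 0.15 × 0.20 = 0.030.
- If the shares were 45% v 40%: 0.05 × 0.05 = 0.0025, up to 0.05 × 0.20 = 0.010.
- With equal shares and an equal shift: 0.
- Spurious QALY difference = shift × difference in time after placement: 0.182 × 0.05 = 0.009, up to 0.182 × 0.20 = 0.036. With the stated 55 days: 0.151 × 0.05 = 0.008, up to 0.151 × 0.20 = 0.030.

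The sign favours ATT if the new respondent scores lower and control if higher.

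**Step 4. Scale.** With 225 analysed per arm (500 × 0.90 / 2) and an assumed SD of 0.20 to 0.30, the standard error of the arm difference in EQ-5D is SD × √(2/225) = 0.019 to 0.028. Most of the 0.0075 to 0.030 range lies within about one standard error.

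**The case against.** The strongest reply is that silence is being read as a design. No sentence says that EQ-5D is self-reported. The participant list is not a list of who answers: the CSRI is on it, yet the Cost-effectiveness section takes carer time and tasks from the CSRI. The EQ-5D version and its respondent are administration details that an article commonly leaves to the full protocol. This stands against any statement that self-report has been chosen or that a proxy form is excluded. It does not remove the conflict over assessments after placement, which is in the article's own text, nor the absence of a carer-rated EQ-5D from a carer list that names each scale.

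The Analyses section also promises follow-up data, where possible, from people who leave the study. That softens the abstract's stop, but it does not say that institutionalised participants continue EQ-5D to week 104.

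Three stronger readings are tempting and are not supported:

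- A reader might infer that EQ-5D change is itself co-primary. The primary outcome is cost-effectiveness; EQ-5D is the effect measure in one of its two analysis types, and the other uses days to institutionalisation.
- A reader might infer that the error cannot cancel between arms. The article documents no loss or switching of respondents by arm, and equal switching with an equal shift gives no bias. People who cannot answer from week 0 need have no switch at all.
- A reader might equate lack of capacity with inability to answer EQ-5D. The article ties capacity to consent, which is a different ability.

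Whether the general validity statement extends to this use cannot be checked from the document; it mentions neither capacity nor respondent.

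**Conclusion.** The point holds as a weakness in data collection with an internal conflict attached. The article leaves the EQ-5D respondent open, lists no carer-rated EQ-5D, and ends assessments at institutionalisation in one place while needing EQ-5D through care-home stays in another. The 2-year change and the QALYs may therefore mix health change with loss or change of respondent.

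A difference between arms is possible because the planned placement rates are 50% and 35%. On the abstract's literal text, the nearer risk is loss of EQ-5D after placement, not a switch of respondent. Size and direction cannot be derived from the document. The 0.009 to 0.036 QALY range rests on an assumed shift, on switching only at placement, on constant hazards and on no deaths; it shows scale and is not an estimate of bias. The change is worth making because it is cheap and cannot be made retrospectively.

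**What to change.** 1. In Assessments, name the EQ-5D respondent and version at every visit. Where there is a carer, collect a carer-rated EQ-5D on the participant at week 0 and each later visit, alongside self-report whenever the participant can give it.
2. Reconcile the abstract with Cost-effectiveness, so that EQ-5D continues to week 104 after placement.
3. In Cost-effectiveness, compute change and QALYs within one respondent series per person. Never subtract one respondent's baseline from another's follow-up.
4. Pre-specify which series is the base case and report the other as a sensitivity analysis. The choice is open to argument, and the document does not settle it.

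The cost is a few minutes of carer time per visit for carers who are already assessed, visits or contact after placement, and one analysis rule. Carer ratings would be unblinded, even at week 0 because the first assessment follows randomisation, and may be affected by carer burden, which ATT is hypothesised to reduce. The inclusion criteria require no carer, so participants without one have self-report only. The trial is in progress, so anyone enrolled without a week-0 carer form cannot have a full carer series.

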### Secondary outcome measures

#### Burden in carers

We will measure both burden associated with care-giving and levels of psychological distress among the principal carers of participants at baseline, 12, 24, 52 and 104 weeks using the 22-item short version of the ZBI
[35].

#### Quality of life

We will measure health-related quality of life in carers using the SF-12v2
[38].

#### Number and severity of serious adverse events

As in any trial, serious adverse events (requiring GP or hospital care) will be recorded and reported. Details of how we propose to do this are presented below in Sect. 6, which deals with safety monitoring procedures.

#### Quantitative and qualitative data

Data on acceptability, applicability and reliability of ATT intervention packages will be collected using the SUTAQ. This questionnaire is currently being validated using data from the WSD. We will collect unpaid carers’ experiences, which will provide examples of ways in which their lives, well-being and care-giving roles may have been enhanced and/or undermined by the use of these technologies. Variation in their experiences and the reasons for this variation will be explored through semi-structured interviews with individuals from groups purposively sampled to maximize diversity of types of carer characteristics from: (1) carers who have used the ATT for at least 6 months, (2) carers who have requested ATT withdrawal after installation and (3) carers who have refused ATT when offered. To achieve theoretical saturation (the point at which no new themes emerge), at least ten participants will be interviewed from each group, with up to a further five from each if needed
[43].

### Statistics

#### Sample size calculation

On average, 50% of participants with a BADLS score of >15 will enter residential care after 24 months
[44]. A reduction in the estimated 24-month transition to care home rate by 30% (i.e. 50% institutionalised at 2 years reduced to 35%) would require the involvement of 500 participants allowing for 10% attrition due to death while still living in a community setting. This equates to an average of 55 days of longer independent home life for participants receiving ATT. The trial would therefore be powered to detect a mean institutional delay of a little less than 8 weeks. Expert opinion suggests that 8 weeks is close to the minimum clinically important difference in delaying institutionalisation
[45].

#### Analyses

Statistical analysis will be by intention to treat (ITT). All participants who are randomised will be included in the comparison and analysed according to their randomised allocation, including those who discontinue the ATTILA study. Wherever possible, we will continue to collect follow-up data from these participants after they leave the study, so that the data set will be as complete as possible.

The primary outcome of time to institutionalisation will be analysed using standard log rank methods and will include all events, even those occurring after 2 years. Continuous outcome measures, e.g. health-related quality of life and functional ability measures, will be analysed using repeated measures regression techniques to maximise statistical power. Exploratory subgroup analyses will be undertaken, with appropriate caution, to investigate any influence of the baseline prognostic factors (gender, age, risk profile, support structure) on outcome.

For qualitative data, thematic analysis of transcripts and field notes will be undertaken to develop themes emerging inductively from data and narrative analysis of longitudinal elements to identify and contextualise acceptable and less-acceptable practices and features of AT equipment use. A collaborative analytic strategy will involve appropriate research team members and service user/carer researchers to enhance validity and to help integrate qualitative and quantitative findings. This component will be subject to a supplementary application for ethical review.

Local, site-specific reports will be produced by each local ATTILA research site towards the end of the fieldwork period. The timing of reports and locally specific content will be locally discussed and negotiated between the local PI and designated senior managers within the local CASSR.

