## Methods

### Design

ATTILA is a pragmatic randomised controlled trial over 104 weeks. Blinding will not be undertaken as it is not feasible. It will be conducted in the homes of people living with dementia and who are eligible to receive a package of social care through CASSRs. The trial will compare outcomes in two groups of participants randomised to one of two study arms: either (1) receiving an ATT needs assessment, followed by the installation of ATT devices and response services which will be deployed by the CASSR, or (2) receiving a semi-structured ATT needs assessment, followed by the installation of an ATT package restricted to only smoke and carbon monoxide detectors and a pendant alarm if indicated, also arranged by CASSRs. The key outcomes will be *time to institutionalisation* and *cost-effectiveness* of the intervention.

The trial is not funded to source, assess the need for or deploy ATT. Our approach is therefore to work alongside CASSRs that have been charged by the Department of Health with responsibility for establishing and developing local ATT services.

The study has been approved by the NHS Health Research Authority National Research Ethics Committee (REC reference number 12/LO/186) and is registered with the ISRCTN (http://www.controlled-trials.com/ISRCTN86537017).

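### The primary log-rank analysis counts events after 2 years although scheduled follow-up ends at week 104; unless everyone is followed to one common date, the estimate can be biased

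*Protocol article*

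**What the plan says.** The Analyses section of the protocol article states that time to institutionalisation "will be analysed using standard log rank methods and will include all events, even those occurring after 2 years". Other sections give a shorter horizon:

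- Design: "ATTILA is a pragmatic randomised controlled trial over 104 weeks". The same section says the trial is not blinded.
- Assessments: "Assessments will be undertaken by local investigators employed by the ATTILA team in weeks 0 (baseline), 12, 24, 52 and 104".
- Abstract, Method/design: "Assessments will be undertaken in weeks 0 (baseline), 12, 24, 52 and 104 or until institutionalisation or withdrawal of the participant from the trial".
- Cost-effectiveness, for the same outcome: "days from randomisation to institutionalisation in the two year period".
- Sample size calculation: "50% institutionalised at 2 years reduced to 35" (per cent).

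The abstract words the study hypothesis differently again: "fewer people in the ATT group will go into institutional care over the 4-year period for which the study is funded".

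The Analyses section also promises to go on collecting follow-up data where it can, but that sentence concerns people who discontinue the study. It does not cover participants who complete week 104 at home. For them the article names no later contact, data source or common end date.

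**The concern.** A log-rank test compares, at each event time, the person who has the event with everyone still under observation and event-free. After week 104 the article says that events count, but it schedules nothing that would show who remains at home.

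Suppose a late admission enters the data when it becomes known, while a participant without one is last confirmed at home at week 104. The risk set after week 104 then contains only people who go on to have the event. Comparing arms within that group says little about the treatment effect, so the late events dilute the contrast built up over the first 2 years. A rule meant to add information could lower power.

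There is a second route to bias. If everyone is assumed at home until a cut-off unless reported otherwise, the late part depends on reporting, and in an unblinded trial reporting may differ between arms.

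This is the main analysis of one of the two primary outcomes.

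**Working it through.** **Inputs from the article.** 50% v 35% institutionalised at 24 months; 500 participants in two arms; 10% attrition due to death; last assessment at week 104, that is 104 × 7 = day 728; 4-year funded period.

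**Assumptions (not stated in the article).** Two-sided alpha 0.05, 90% power, 1:1 allocation, exponential times, uniform recruitment over 2 years with a data cut at 48 months.

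**Step 1: the plan's own figure.** Under proportional hazards, HR = ln(0.65)/ln(0.50) = 0.621. The two-proportion formula with pooled variance under the null gives 454 in total; 454/0.9 = 505, and 454 × 1.1 = 499.4, rounded up to 500. Schoenfeld's formula gives 186 events; 186/0.425 = 438; 438/0.9 = 487. Freedman's gives 193 events; 193/0.425 = 455; 455/0.9 = 506. All lie within 3% of 500. At 80% power, two-sided, the total would be only 365 to 407, so 90% is the natural reading. The 500 therefore fits the 24-month landmark and does not need late events.

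**Step 2: how time after week 104 is handled.** Two configurations, each with 2,000 simulated trials per scenario: (A) 225 per arm, without deaths; (B) 250 per arm, with 10% deaths per 2 years treated as censoring. True HR is 0.621. The censoring point in the first row is 24 months in A and day 728 in B.

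| Handling after week 104 | A: HR, power | B: HR, power | B: events (late) | B: type I error |
|---|---|---|---|---|
| All censored at 2 years | 0.623, 90.9% | 0.621, 92.7% | 203 (0) | 4.8% |
| All followed to a common date | 0.621, 95.4% | 0.619, 96.4% | 260 (57) | 4.6% |
| All late events added, event-free stop at week 104 | 0.682, 85.1% | 0.680, 87.2% | 259 (57) | 5.7% |
| Half of late events added, event-free stop at week 104 | 0.654, 87.7% | 0.651, 89.0% | 231 (29) | 5.0% |
| Event-free carried to the cut-off, half of late events found in each arm | not run | 0.622, 94.1% | 231 (29) | 4.3% |

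A separate run with 250 per arm and the same recruitment and cut-off gave the same pattern: HR 0.65 to 0.68 and power 87 to 90% with late events only, 0.62 and 93% with censoring at 24 months, 0.63 and 97% with a common date.

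**Step 3: hand check of the dilution.** If late events carried no treatment contrast at all, the pooled log hazard ratio would shrink by the share of early events. With all late events: (259 − 57)/259 = 0.780; 0.780 × ln(0.621) = 0.780 × (−0.476) = −0.371; exp(−0.371) = 0.69. With half: 202/231 = 0.874; 0.874 × (−0.476) = −0.416; exp(−0.416) = 0.66. The simulated 0.68 and 0.65 are close to these, which supports the explanation.

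**Step 4: unequal capture between arms.** Configuration B, event-free participants carried to the cut-off, capture rates assumed:

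| Late events found, control / ATT | HR if true HR is 1 (type I error) | HR if true HR is 0.621 |
|---|---|---|
| 70% / 50% | 0.95 (6.8%) | 0.59 |
| 50% / 70% | 1.05 (6.5%) | 0.66 |
| 90% / 50% | 0.91 (13.0%) | 0.56 |
| 50% / 90% | 1.11 (13.7%) | 0.69 |

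**The case against.** The strongest reply is that counting all events is ordinary practice. With staggered entry, each participant is followed to the analysis date and censored there, and early recruits naturally contribute more than 2 years. On that reading the risk set is valid and the rule beats truncation: power is 95 to 97%, against 91 to 93%. The week 0 to 104 visits are occasions for rating scales and need not be the only source of an admission date; the Case accountability section says that care services will be recorded. A cut-off date is commonly left to the analysis plan, which is not shown. Even in the adverse scenario the shift is towards no effect and type I error holds.

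Much of this stands. A reader might infer that the hazard ratio is distorted. The article does not support that: it nowhere says that late events and event-free time are ascertained differently, and it names a log-rank test without a hazard ratio. A reader might also infer that a 4-year hypothesis cannot be tested because few participants are at risk for 4 years. That is not supported either. The phrase can mean the calendar period of funding, no recruitment period is given, and the hypothesis under Aim of the study carries no horizon. A 24-month rate is also a normal planning landmark for a time-to-event trial.

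What the reply does not remove is a conflict between two things the article states. It says that events after 2 years count, and it sets a 104-week trial with assessments ending at week 104. This is more than an omitted detail. The ordinary reading needs everyone to be followed to a common date, and the schedule as written does not provide for that.

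**Conclusion.** The point holds in conditional form. The open-ended event rule does not fit the 104-week schedule or the 2-year windows used elsewhere, and the outcome of the primary analysis depends on how the gap is filled. Adding late events while event-free people stop at week 104 moves a hazard ratio of 0.62 to about 0.65 to 0.68. It cuts power from about 91 to 93% to 85 to 90%, with type I error near 5%. Unequal late capture can push the estimate either way, with type I error of about 7 to 14% at the capture rates assumed here. Equal, complete follow-up to a common date removes the problem and raises power.

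These sizes rest on assumed 2-year recruitment, a 48-month cut, exponential times and 1:1 allocation. The sample size of 500 is not affected. Because this is a primary analysis and the repair is cheap, the text should be changed.

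**What to change.** In the Analyses section, count institutionalisations after week 104 only up to one common calendar cut-off date. Obtain residence and vital status at that date in the same way for every randomised participant in both arms, for example from CASSR records or one call to the carer. Censor event-free participants at that date, and report an analysis censored at day 728 as a sensitivity analysis. If this status cannot be obtained for nearly all participants, censor everyone at day 728 in the primary analysis.

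The cost is a wording change and one status check per participant. The data-sharing arrangements under Recruitment/consent procedures and Release of personal data by the CASSR are described mainly for recruitment and contact details, so whether they cover a late status check must be confirmed. The fallback needs no new data, but it gives up the late events (57 of 260 in configuration B) and a few points of power compared with complete follow-up: 91 to 93% instead of 95 to 97%.

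### The abstract stops assessments at institutionalisation while the Methods schedule carers to week 104; under the abstract's rule the carer comparison is cut off by the primary outcome

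*Protocol article*

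**What the plan says.** The protocol article gives two timetables.

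- **Abstract, Method/design:** "Assessments will be undertaken in weeks 0 (baseline), 12, 24, 52 and 104 or until institutionalisation or withdrawal of the participant from the trial".
- **Methods, Assessments:** "Assessments will be undertaken by local investigators employed by the ATTILA team in weeks 0 (baseline), 12, 24, 52 and 104". No stop at placement is mentioned, and unpaid carers are put on the same timetable.
- **Burden in carers:** burden is measured, with "levels of psychological distress among the principal carers of participants at baseline, 12, 24, 52 and 104 weeks". Again there is no stop at placement. The Quality of life section adds the SF-12v2 for carers.
- **Cost-effectiveness:** the second economic analysis covers the whole two years, care home stays included, with EQ-5D change as its outcome. It needs participant data after placement.

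For the analysis, the Analyses section states: "Continuous outcome measures, e.g. health-related quality of life and functional ability measures, will be analysed using repeated measures regression techniques to maximise statistical power". The same section specifies intention to treat and continued follow-up, where possible, of participants who leave the study. Handling of missing data bases its sensitivity analyses on reasons for withdrawal and on stopping the intervention; placement is not named.

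The fourth hypothesis (Aim of the study) and secondary objective 2 concern lower burden and stress in unpaid carers. Neither is limited to the time the participant lives at home. The sample size section plans on "50% institutionalised at 2 years reduced to 35" per cent.

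**The concern.** When assessments stop is a data-collection rule. If sites follow the abstract, a carer's ZBI and SF-12v2 series ends when the participant is placed. Placement is the primary outcome and is planned to differ by arm, so the carer data would be truncated by the event the intervention is meant to delay, and more often in the control arm. No later analysis plan can recover scores that were never collected.

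A repeated measures regression on what remains compares carers of participants at home with carers of participants at home. Depending on the model, it estimates an effect while at home or an effect as if nobody were placed. The contrast between a carer still caring at home and a carer whose relative has moved into a care home does not enter. Delayed placement acts on carers partly through that contrast, so the result would not answer the hypothesis about carers as stated. If sites follow the Methods, the scores exist and the abstract is wrong. If sites differ, the data will be a mixture of the two.

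**Working it through.** **1. The plan's own figures.** The article states no alpha or power. With two-sided 5% and 90% power (assumed), comparing 50% with 35% needs 227 per arm, 454 in total. Allowing 10% attrition gives 454 / 0.9 = 505, or 454 x 1.1 = 500 after rounding up, in line with the stated 500. The stated 55 days also reproduces: 0.15 x 730 / 2 = 54.75, taking placement as linear over two years. The planning rates can therefore be used as the trial's own. No effect size, SD or power is given for the carer outcomes, so there is no carer figure to reproduce.

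**2. Week-104 carer scores lost if assessment stops at placement.** This assumes that participants with a carer are placed at the planning rates.

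| | Control | ATT |
|---|---|---|
| Placed by week 104, so no score | 50% | 35% |
| Still at home | 50% | 65% |
| Still at home after 10% attrition | 0.9 x 0.50 = 45% | 0.9 x 0.65 = 58.5% |

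The 15-point imbalance is the planned treatment effect itself.

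**3. At-home effect against all-carer effect at week 104.** Let m be mean burden at home in the control arm, d the reduction due to ATT while at home, and R the fall in burden after placement. Both d and R are assumed. Deaths are ignored, R is taken as equal in the two arms, and there is no selection.

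- Control, all carers: 0.50m + 0.50(m - R) = m - 0.50R
- ATT, all carers: 0.65(m - d) + 0.35(m - R) = m - 0.65d - 0.35R
- All-carer difference, ATT minus control: **-0.65d + 0.15R**
- At-home difference: **-d**

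The signs differ when 0.15R > 0.65d, that is R > 4.33d.

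| d | R | At-home difference | All-carer difference |
|---|---|---|---|
| 0.10 SD | 0.3 SD | -0.10 | -0.065 + 0.045 = -0.02 |
| 0.10 SD | 0.5 SD | -0.10 | -0.065 + 0.075 = +0.01 |
| 0.10 SD | 0.8 SD | -0.10 | -0.065 + 0.120 = +0.055 |
| 0.10 SD | 0 | -0.10 | -0.065 |

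Even with R = 0 the two effects differ, but then the sign does not change.

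**4. Earlier visits.** At week 52, linear placement leaves 75% (control) and 82.5% (ATT) at home, so reversal needs R > 0.825 / 0.075 = 11d. A constant hazard leaves 70.7% and 80.6%, and reversal needs R > 8.1d. The gap is mainly a late-visit matter.

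**5. Selection.** Suppose the most burdened households are placed first and ATT has no effect on burden. ATT then keeps more of them in the at-home sample. With an assumed correlation of 0.5 to 0.9 between burden and placement, the raw at-home mean at week 104 is 0.11 to 0.20 SD worse under ATT. This bias runs against ATT, opposite to the reversal in step 3.

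**The case against.** The strongest reply is that the article never restricts the carer models to time at home. The Analyses section says intention to treat and promises continued follow-up where possible. The Methods schedule carers to week 104, and the two-year economic analysis needs contact with participants after placement. On this view the abstract's clause is loose shorthand, and the handling of placement in the model belongs to an analysis plan that is not shown. Burden while caring at home is also a legitimate question.

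Much of this stands. The restriction comes from one clause in the abstract, not from the analysis sentence, and the form of the model can be left to an analysis plan. What does not fall away is the contradiction over when data collection ends. The promise of continued follow-up concerns participants who leave the study; it names neither carers nor placement.

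A reader might infer two stronger claims that the article does not support.

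- *That longer caring is left out altogether.* It is not. Burden during the extra time at home is scored at the visits, and carer time is valued in the societal cost perspective. What would be lost is the scores after placement.
- *That ATT will be reported as easing carers when they gain nothing.* This needs a true at-home benefit and a fall after placement more than about 4.3 times as large; neither figure is in the article, and selection can push the other way. A benefit of 0.10 SD would also seldom reach significance. With 45% and 58.5% of 250 per arm scored, the single-visit standard error is sqrt(1/112.5 + 1/146.25) = 0.125 SD, giving about 12% power before baseline adjustment.

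**Conclusion.** The point holds as an unreconciled contradiction with a consequence for the carer outcomes. If the abstract's rule is followed, about 50% of control and 35% of ATT carers have no week-104 score because of placement, before deaths, and the planned regression does not estimate the effect on carers overall. The at-home and all-carer effects then differ (-d against -0.65d + 0.15R) and can differ in sign. The size and direction of the gap rest on assumed values and cannot be settled from the article. The missing-score shares rest on the article's own planning rates, taken to apply to participants with a carer. If the Methods timetable is followed, the data exist, and what remains is to correct the abstract and say which carer comparison is meant. The primary outcome is not affected.

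**What to change.** Reconcile the abstract with Assessments, Cost-effectiveness, Burden in carers and Analyses:

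1. State that carer questionnaires continue at 12, 24, 52 and 104 weeks wherever the participant lives.
2. Define the carer comparison by allocated arm, over carers of all randomised participants alive at each visit, with scores after placement included. Report deaths and placements by arm beside it.
3. Label any at-home-only analysis supplementary, and do not present it as evidence of benefit to carers overall.

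The cost is a few sentences, plus telephone or postal follow-up of carers after placement: on the planning rates, up to 35% to 50% of carers by week 104. The time points are already in the Burden in carers schedule. The wording of the model can be settled later; the collection rule cannot, because missed scores are not recoverable.
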